##### Secondary Outcome Analysis

For continuous outcomes (i.e., QoLi-20, CSI, SF-36, and EQ-5D VAS), we will define change from baseline to 6-month follow-up as scores at 6 months minus scores at baseline. We will conduct analyses of covariance (ANCOVA) to compare changes from baseline between CATCH-FI and CATCH-UC, adjusting for baseline scores as a covariate.

For count outcomes (i.e., GAIN-SS, number of hospitalizations, number of days hospitalized, and number of emergency department visits) we will model the baseline and 6-month outcomes using generalized estimating equations (GEE) assuming the Poisson distribution or the negative binomial distribution, if over-dispersion is suggested by the data. The models will include the main effects of group (CATCH-FI vs. CATCH-UC) and time (6 months vs. baseline), and the interaction of group by time. A significant interaction will indicate that change from baseline is different between the groups. Rate ratios and 95% confidence intervals will be estimated.

The analysis of administrative data is similar to that of count outcomes, except that the period of consideration will be 12 months instead of 6 months pre and post-randomization.

For analyzing the number of days stably housed in the past 6 months, we will consider GEE with a Poisson or negative binomial distribution. The model will include the main effects of group and time, an interaction between group and time, selected covariates, and an offset represented by the natural log of residence days accounted during the 6 months interval. Rate ratios and 95% confidence intervals will be estimated to compare the rate of days stably housed per person-months.

For the WAI-SR, evaluated at the 6-month follow-up only, total scale, and sub-scales scores will be calculated and compared between the groups using the two-sample *t*-test or the Wilcoxon rank-sum test if extreme outliers are present. The correlation between WAI-SR and other outcomes at 6 months will be explored by estimating the Pearson or Spearman correlation coefficients, overall and by group.

SAS 9.4 will be used for all analyses and all analyses will use the intention-to-treat principle. We will consider multiple imputation to handle missing data. All statistical tests will be two-sided and a *p*-value of 0.05 or less will indicate statistical significance. There are no plans for interim analyses.

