### Study Participants: Recruitment, Eligibility, and Randomization

The CATCH program receives 450–600 referrals of homeless adults per year, from hospitals or community agencies, prior to or shortly after hospital discharge for a mental health condition. Study participants were recruited among successive new CATCH program participants. Referrals to the study were made by CATCH staff during program intake meetings. Program participants expressing an interest in receiving information about the study were contacted by research staff to confirm interest, eligibility, to obtain informed consent, and to conduct a baseline assessment.

Study participants meet both CATCH program and CATCH-FI study eligibility criteria. Program eligibility criteria include: (1) current homelessness (defined as having no fixed place to stay for at least the past seven nights with little likelihood of finding a place in the upcoming month) or precarious housing (defined as currently occupying a single room in a multi-tenant building or house with shared common areas including bathroom and kitchen or a hotel/motel as a primary residence, and having a history of one or more episodes of absolute homelessness in the past year); (2) service provider-determined unmet mental health needs; (3) service user-determined unmet support needs; and (4) age 18 years or older. Excluded from the program are individuals with recent aggressive behavior requiring a higher intensity of support, or individuals whose illness severity necessitates residential care. To be eligible for the current study, in addition to meeting program eligibility requirements, participants must have been new referrals to CATCH, recently admitted or readmitted to hospital services, and have had at least one contact with the CATCH team.

Participants were randomized following the baseline interview using block randomization (55), which randomizes the participant list into groups 1:1 using blocks of four and six. This approach has the advantage of maintaining balanced group sizes throughout the recruitment process. The nature of the intervention precluded blinding of participants and study staff.

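### Count and housing outcomes are tested by a group-by-time interaction with a free baseline group difference: valid, but usually less precise than the baseline adjustment already used for the continuous outcomes

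*Protocol article*

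**What the plan says.** All of this is in the protocol article, mostly under Secondary Outcome Analysis.

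- **Count outcomes** (GAIN-SS, hospitalisations, hospital days, emergency visits): "we will model the baseline and 6-month outcomes using generalized estimating equations (GEE) assuming the Poisson distribution or the negative binomial distribution". The terms begin "The models will include the main effects of group (CATCH-FI vs. CATCH-UC) and time (6 months vs. baseline"), and their interaction is added. The test is named: "A significant interaction will indicate that change from baseline is different between the groups".
- **Administrative counts**, over 12 months before and after randomisation: "The analysis of administrative data is similar to that of count outcomes".
- **Days stably housed**, where a GEE is put forward for consideration: "The model will include the main effects of group and time, an interaction between group and time, selected covariates, and an offset".
- **Continuous outcomes** are handled differently. ANCOVA is used "to compare changes from baseline between CATCH-FI and CATCH-UC, adjusting for baseline scores as a covariate".
- **Timing of allocation**, under Study Participants: "Participants were randomized following the baseline interview using block randomization".

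**The concern.** Baseline values precede allocation, so any baseline difference between the arms is chance. A model with a free group main effect estimates that difference anyway, and the interaction subtracts it in full on the log scale. Baseline sampling noise therefore enters the treatment estimate. Baseline adjustment subtracts only the part of the chance difference that predicts follow-up, which is what the ANCOVA in the same section does.

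Precision in the health service use, substance use and housing comparisons is at stake. The first research question and the study hypothesis name health, health service use and housing. The trial was sized on the primary outcome alone, so no power was planned for these comparisons.

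**Working it through.** **1. The plan's own figure.** The only sample size given is for the primary outcome. The Signorini formula with 1:1 allocation, 4.6 contacts per month and rate ratio 1.25 gives N = [1.96·√4 + 0.8416·√(1/0.5 + 1/(0.5·1.25))]² / (4.6·(ln 1.25)²) = 132.9. That is 66.4, rounded up to 67 per group. Allowing for attrition, 67/(1 − 0.22) = 85.9, so 86 per group and 172 in total. This reproduces the article and does not involve the secondary models.

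**2. Inputs for the comparison.** The model terms and the timing of randomisation come from the article. Three quantities do not and are assumed: rho, the correlation of baseline and follow-up counts; CV0 and CV1, their coefficients of variation; and k = CV0/CV1.

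**3. Variances.** With two time points, complete data and no extra covariates, the GEE interaction is the log ratio of follow-up means minus the log ratio of baseline means. With n per arm and no large treatment effect:

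- interaction: (2/n)·(CV1² + CV0² − 2·rho·CV0·CV1)
- baseline-adjusted: (2/n)·CV1²·(1 − rho²)

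The ratio is R = (1 + k² − 2·rho·k)/(1 − rho²) = 1 + (k − rho)²/(1 − rho²). It cannot fall below 1, and equals 1 only when k = rho. At k = 1 it reduces to 2/(1 + rho).

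**4. Values of R.**

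| k | rho 0.2 | rho 0.4 | rho 0.6 |
|---|---|---|---|
| 0.7 | 1.26 | 1.11 | 1.02 |
| 0.85 | 1.44 | 1.24 | 1.10 |
| 1 | 1.67 | 1.43 | 1.25 |
| 1.2 | 2.04 | 1.76 | 1.56 |
| 1.5 | 2.76 | 2.44 | 2.27 |

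At k = 1 and rho 0.8, R is 1.11. A loss of 30–60% at k = 1 needs rho between 2/1.6 − 1 = 0.25 and 2/1.3 − 1 = 0.54. Over that range, 67 per arm under the interaction test carry the precision of 67·(1 + rho)/2, or about 42 to 52 per arm under adjustment.

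**5. Against ignoring baseline.** At k = 1 the interaction has 2(1 − rho) times the variance of a follow-up-only comparison. Below rho 0.5 it is the less precise of the two.

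**6. Simulation, 67 per arm.** Over-dispersed counts were generated, and the interaction was compared with a Poisson model adjusted for log baseline (1,500 trials per setting). Variance ratios were 1.66 (rho 0.17), 1.52 (0.32), 1.42 (0.43), 1.30 (0.56) and 1.17 (0.75), with 1.04 (0.72) in a heavy-tailed setting. A separate run took mean visits falling from 3 to 1.5 and latent CV 1. It gave ratios of 1.62, 1.43 and 1.31 at latent correlation 0.2, 0.4 and 0.6. Power for a rate ratio of 0.65 was 34%, 39% and 40% with the interaction, against 47%, 50% and 50% with adjustment.

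**7. Admissions with a floor.** Study entry required a recent admission or readmission. Baseline admissions were set to at least 1, with mean 2 falling to 0.8 and latent CV 1. The ratio was 1.17, 1.03 and 0.99 at latent correlation 0.2, 0.6 and 0.9. The last value amounts to no loss.

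**The case against.** The strongest reply is that nothing here is wrong. Under randomisation the interaction test is valid, it is widely used, and the article says plainly what it measures. Only secondary outcomes are touched. That stands: a reader might infer bias from the carried-over baseline imbalance, but the imbalance is chance and averages to zero, so the cost is in precision only.

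A reader might also infer a flat loss of 30–60% for every outcome. The article does not support that. It gives no correlation or dispersion, and one range cannot cover outcomes that may move in opposite directions. The recent-admission criterion may narrow baseline spread for admissions (k below 1, small loss). Homelessness at entry may widen relative baseline spread for housed days (k above 1, larger loss). Both directions are assumptions.

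Three narrower replies also have force.

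- Removing the group main effect is not automatically the same as baseline adjustment. Under an independence working correlation, the common baseline mean and the two follow-up means are estimated separately. The result is then the follow-up-only rate ratio.
- A follow-up-only outcome model drops participants without follow-up unless they are imputed, and 22% attrition is expected.
- The housing model is worded as something to be considered, with covariates still to be chosen.

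All three shape the fix. None removes the point: the interaction with a free group effect is stated as the rule for the count outcomes, and the section already accepts baseline adjustment for the continuous ones.

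**Conclusion.** The point holds as a loss of efficiency in secondary outcomes. The planned test is valid, but in large samples it is never more precise than baseline adjustment and usually less so.

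The size rests on assumed values. With similar relative spread at both times, the extra participants needed are 67%, 43%, 25% and 11% at rho 0.2, 0.4, 0.6 and 0.8. For admissions, the loss may run from near zero to about 17–26% if the entry criterion narrows baseline spread. For housed days it may exceed the equal-spread figures; k = 1.2 gives 56–104% over rho 0.6 to 0.2.

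Adjustment would not make these comparisons well powered: in the simulated visits example, power still only reaches 47–50%. The primary outcome analysis and the 172 participants are unaffected.

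**What to change.** For each count outcome, make the main test the group rate ratio at follow-up: 6 months for self-reported counts and GAIN-SS, 12 months for administrative counts. Estimate it from a Poisson or negative binomial model with robust standard errors, containing group and log(baseline count + 1). For days stably housed, use the baseline housed-day rate as the covariate and keep the offset for days accounted for. Keep the multiple imputation that the article says will be considered, so that participants without follow-up are not simply dropped.

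Alternatively, keep the GEE on both time points without the group main effect, so that the arms share one baseline mean. State an exchangeable or unstructured working correlation, because under independence this model ignores baseline.

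The cost is analysis-plan wording only; no new data are needed. The article describes follow-up as still running and the analyses as still to come, so the change could be fixed before outcomes are compared by arm.

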### Study Design

Using a community-based, participatory research framework, CATCH-Financial Incentives (CATCH-FI) is a pragmatic field trial using mixed methods to evaluate the impact and acceptability of financial incentives in promoting service engagement of homeless adults with mental illness following hospital discharge. This study was launched in December 2018. Study recruitment is completed, data collection however is ongoing and the trial is registered with ClinicalTrials.gov (Identifier: NCT03770221).

CATCH program participants enrolled in the CATCH-FI trial and randomly assigned to the intervention arm receive $20 for every week they remain meaningfully engaged with program service providers over 6 months of follow-up, or until they are successfully transitioned to longer-term supports. Study participants can earn up to $80CAN per month by attending meetings with their program service provider by phone, text, email, or in-person, as per their care plan. Participants randomly assigned to the control arm receive usual CATCH care, which does not include a financial incentive for attending meetings with their program service provider.

The impact of financial incentives on participants' level of service engagement, measured by program attendance, evaluated as the number of “health-care contacts” a participant makes with CATCH service providers over a 6-month follow-up period. Of note, participant contacts with service providers are counted as “health-care contacts” if they relate to participants' care plans. As a low barrier program, CATCH service providers meet program participants in person, via phone, email, or texts, as per program participants' needs and preferences. Social or trivial contacts of program participants with service providers are not considered “health-care contacts” and are not being measured or documented in program records or reports to program funders.

Secondary health, health service use, quality of life, and housing outcomes (secondary outcomes) are also being collected over the study period. The study hypothesis is that participants receiving financial incentives will have higher levels of service engagement and consequently better health, health service use, quality of life, and housing outcomes compared to participants receiving usual care.

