**Health service use**		
	Self-report	Self-reported number of emergency department visits, hospital admissions, and days in hospital in the past 6 months for pre- and post-randomization.
	ICES administrative data linkage^a^	Number of emergency department visits, hospital admissions, and physician visits in the 12 months pre- and post-randomization.

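### One unadjusted 0.05 significance rule covers 13 to 14 secondary between-group tests (17 with the WAI-SR subscales), and none is labelled supportive or exploratory

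*Protocol article*

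**What the plan says.** The Protocol article names one primary outcome, the count of contacts with program providers (Quantitative Measures), and sizes the trial on it alone (Sample Size). The decision rule comes at the end of Secondary Outcome Analysis and is not limited to the primary: "All statistical tests will be two-sided and a *p*-value of 0.05 or less will indicate statistical significance". For the count outcomes the same section adds: "A significant interaction will indicate that change from baseline is different between the groups".

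The Study Design section puts the secondary outcomes into the study hypothesis. The incentive arm is expected to engage more and to have "consequently better health, health service use, quality of life, and housing outcomes compared to participants receiving usual care".

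The list of comparisons is long. Beyond the continuous and self-reported count outcomes, the WAI-SR is handled so that "total scale, and sub-scales scores will be calculated and compared between the groups", and Table 1 adds linked administrative outcomes: "Number of emergency department visits, hospital admissions, and physician visits in the 12 months pre- and post-randomization".

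The article describes no adjustment for the number of secondary tests and no order among them. It applies the word exploratory only to descriptive work at the start of Quantitative Analyses. The correlations of the WAI-SR with other outcomes are also to be explored. Neither statement covers the secondary group comparisons.

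**The concern.** A 5% rule applied separately to each of many outcomes does not hold the chance of a false finding across the set at 5%. That matters less when the outcomes are presented as supportive. Here they are part of the hypothesis, and a p-value at the threshold is said to indicate an effect.

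The article also leaves open which measure speaks for a domain. Only housing has a named main measure (days stably housed, Table 1). Emergency visits and admissions each appear twice, by self-report over 6 months and by linkage over 12 months, and neither source is named as deciding. A conclusion that incentives improved health, service use or quality of life could then rest on one chance result in a list of 14 or more.

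**Working it through.** **1. The primary is sound on this point.** Inputs from Sample Size: usual-care rate 4.6 contacts per month, rate ratio 1.25, 80% power, two-sided 0.05; 1:1 allocation from the randomization paragraph. The Poisson formula for a binary covariate, with one month of exposure and no overdispersion, is

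N = (z₀.₉₇₅·√V₀ + z₀.₈₀·√V₁)² / (4.6·(ln 1.25)²), with V₀ = 4 and V₁ = 2 + 2/1.25 = 3.6.

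This gives N = 132.9, or 66.4 per group, so 67 as stated. Allowing for attrition, 67/(1 − 0.22) gives 86 per group and 172 in total, also as stated. The two-sided 0.05 level is used consistently for the primary, and nothing below changes it.

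**2. Count of secondary between-group tests** (Secondary Outcome Analysis read with Table 1):

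| Domain | Tests | Number |
|---|---|---|
| Health | CSI, SF-36 PCS, SF-36 MCS, GAIN-SS | 4 |
| Service use | self-reported admissions, hospital days, emergency visits; linked emergency visits, admissions, physician visits | 6 |
| Quality of life | QoLi-20, EQ VAS | 2 |
| Housing | days stably housed | 1 |
| **In the hypothesised domains** | | **13** |
| Working alliance | WAI-SR total | 1 (total **14**) |
| | WAI-SR task, goal, bond | 3 (total **17**) |

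Table 1 mentions two further substance-use outcomes (days with problems, money spent). These are not counted, nor are any tests on single QoLi-20 scales.

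**3. Independent tests, no secondary effect anywhere.** The chance of at least one significant result in either direction is 1 − 0.95ᵏ. A two-sided 0.05 test leaves 0.025 in the direction of benefit, so the chance of at least one false benefit is 1 − 0.975ᵏ.

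| k | Any false significant result | At least one false benefit |
|---|---|---|
| 13 | 48.7% | 28.1% |
| 14 | 51.2% | 29.8% |
| 17 | 58.2% | 35.0% |

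**4. Correlated tests.** The article gives no correlations, so a common correlation ρ is assumed: Zᵢ = √ρ·F + √(1 − ρ)·Eᵢ, with F and Eᵢ independent standard normal, |Zᵢ| > 1.96 for either direction and Zᵢ > 1.96 for benefit (400,000 draws).

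| ρ | 14 tests: any | 14 tests: benefit | 17 tests: any | 17 tests: benefit |
|---|---|---|---|---|
| 0 | 0.512 | 0.298 | 0.583 | 0.351 |
| 0.3 | 0.438 | 0.225 | 0.493 | 0.254 |
| 0.5 | 0.348 | 0.174 | 0.386 | 0.193 |
| 0.7 | 0.249 | 0.125 | 0.270 | 0.135 |

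**5. Scale.** With 14 tests the false-benefit rate is 0.125/0.025 = 5 times to 0.298/0.025 = about 12 times the directional rate of a single test. The expected number of false benefits is 14 × 0.025 = 0.35, or 17 × 0.025 = 0.43. For a false benefit to be more likely than not, about 28 independent tests would be needed (the first k with 1 − 0.975ᵏ above 0.5).

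**The case against.** The best case for the plan is that unadjusted secondary tests beside one protected primary are a common and defensible design. The 0.05 sentence is a conventional per-test threshold and promises no control across the set. A condensed article may leave secondary multiplicity to an analysis plan. The hypothesis presents secondary benefit as a consequence of better engagement, the research question on outcomes is worded descriptively, and nowhere does the article say that one significant measure settles a domain. The WAI-SR belongs to none of the four hypothesised domains. Self-reported and linked service use cover different windows, so they are not the same test repeated. Rate ratios with confidence intervals are already planned for the count and housing outcomes.

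Much of this stands. The design is acceptable if the secondaries are labelled for what they are. The count without the WAI-SR is 13, and that relies on Table 1 for splitting the SF-36 into two scores. The interaction sentence has a use, because it identifies which model term carries the treatment contrast.

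The appeal to an unseen analysis plan does not stand. The article does not leave the matter open: it states a rule for all tests, and an analysis plan that treated the secondaries differently would contradict it. Removing the WAI-SR changes little, since 13 independent tests still give 48.7% and 28.1%.

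A reader might also infer that the trial has no hierarchy at all. It has one: a single primary outcome, with everything else called secondary. What is missing is any order or status within the secondary set.

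**Conclusion.** The point holds as a defect in a stated rule. It affects the secondary conclusions only. Among 14 secondary tests the chance of some false significant result is about 25% to 51%, and of a false benefit about 12% to 30%. Among 17 the ranges are 27% to 58% and 14% to 35%.

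These figures assume that no secondary effect exists and that all tests share one correlation between 0.7 and 0. Some positive correlation is plausible, because symptoms overlap with quality of life, self-report with linked use, and the WAI-SR total with its subscales. The upper ends are therefore best read as limits within this range.

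A reader might infer that a false secondary benefit is likely. The figures do not support that: the chance stays at or below about 35% throughout, and the values above 50% count false harm together with false benefit. Nor does the article say that a secondary benefit would be claimed if engagement did not improve; it simply has no rule that prevents it. The supported conclusion is that a significant secondary result would be much weaker evidence than the blanket 0.05 rule suggests.

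**What to change.** Change the wording of Secondary Outcome Analysis:

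- Reserve the declaration of statistical significance at two-sided 0.05 for the primary contrast.
- State that all secondary outcomes are supportive, reported as estimates with 95% confidence intervals not adjusted for multiplicity, and that p-values will not be used to declare an effect.
- Reword the interaction sentence, without deleting it, to say that the group-by-time interaction estimates the between-group difference in change.

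This needs no new data or participants and leaves the primary test and the 172 participants unchanged. The article reports data collection as still ongoing, so the wording could be settled before analysis. The downside is that no secondary result can be declared statistically significant on its own.

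If the sponsor wants confirmatory secondary claims, one option is to name one measure per hypothesised domain in advance (one data source for service use), and to test the four by Holm at an overall 0.05 only if the primary is significant. That is a trade-off and not required: the smallest of the four p-values would have to be at most 0.05/4 = 0.0125, and all other secondaries would remain exploratory.
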